## 14.0 BIOSTATISTICS

**14.1 Primary objective:** *To evaluate 3-year DFS survival in patients managed with TNT and TME or NOM, compared with standard historical controls managed according to standard of care (CRT and TME followed by ACT).*

We hypothesize that 85% of patients with LARC treated with TNT and selective NOM will be alive and free of disease at 3 years. The 3-year DFS for similar patients (stage II/III LARC within 6 cm from the anal verge) treated according to the standard of care (CRT, TME, and ACT) is 75%. (Survival data provided by Maas et al from a pooled analysis of 3105 rectal cancer patients treated with CRT and TME). [35] In this trial, each arm is designed as a single-stage study that discriminates between 3-year DFS rates of 75% (historical control) and 85% (Study Arms, INCT and CNCT). No formal statistical comparison of the two arms is planned.

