For our power calculation, we assume uniform accrual over time and an exponential distribution for time to death. Based on our previous experience, we can assume that we will be able to accrue 2-4 patients per arm per month. Using the approach proposed by Lawless (1982), for 86% power, a two-sided type I error of 5% we will require 101 patients per arm. Based on our estimated accrual rate, a total of 202 patients can be accrued over 40 months with an additional 3-year follow-up.[95] With a sample size of 101 patients (each arm), we will consider the treatment regimen of an arm worthy of further study if the 3-year DFS rate exceeds (based on parametric exponential estimate) .82 (the upper critical value). The 3-year rates will be estimated using parametric exponential estimates as well as on Kaplan-Meier estimates. Analysis of the primary endpoint will occur 3 years following the completion of accrual. We anticipate about 10% loss to follow-up (dropouts that occur before the entire regimen has been completed), and will recruit an additional 10 patients per arm to account for this. Patient accrual for the entire trial is expected to take 40 months, with approximately 6 patients (2-4 per arm) per month. We will update the analysis after we have completed follow-up. Accrual has been completed a year ahead of schedule. Preliminary results indicate that we may require additional patients to detect differences in organ preservation rates, one of the secondary aims of this study. Based on this new information, we plan to increase accrual to 325 patients. As accrual has been progressing faster than initially estimated, we expect that, with the proposed increase, accrual will still be completed within the initially proposed accrual period.

This trial could complete with 3 possible results: both arms are worthy of further study, one arm is worthy of further study, no arm is worthy of further design. In all three cases, all Aim 2 analyses will be performed. In the ambiguous case when both the INCT and CNCT arms are worthy of further study, we will use a pick-the-winner strategy based on the number of NOM patients. This is described in more detail in section 14.2.

**14.2 Secondary objective 1.:** *To compare outcomes in patients treated on the two arms of this study, with respect to rates of organ preservation, compliance with the neoadjuvant protocol, and major adverse events.*

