In addition, we will calculate therapy compliance using the following measures: the number of days RT was held, the number of RT delays of  $\geq 1$  week, the number of dose delays and the number of dose reductions in INCT and CNCT. We will also calculate the rate of select hematologic events (as outlined in 17.2), select non-hematologic events (as outlined in 16.0), and unexpected Grade 3 or higher non-hematologic adverse events and surgical complications in each treatment arm. Comparisons will be done using the Wilcoxon Rank Sum test or the Fisher’s Exact test.

**14.3 Secondary objective 2.:** *To measure patient-reported functional outcomes and QoL in patients with LARC treated with NCT, CRT and NOM, and compare these to patients treated with TME.*

The primary analyses for this aim will use data combined across both treatment arms; however, differences according to treatment will also be investigated. The primary endpoint will be QoL as measured one year from the end of TNT. Secondary endpoints will be bowel, sexual, and bladder function. While the subscales will be reported, the primary secondary endpoints will be the total scores on the BFI, FSFI and IIEF. With a total of 325 patients accrued, we expect that 129 patients will obtain complete clinical response and 196 will undergo TME. Approximately 15 to 30 patients initially treated with NOM are expected to cross over to TME at some point during follow-up. For the primary analyses, the NOM group will include these cross-overs on an intent-to-treat analysis. In secondary analysis, patients who eventually crossed over to receive surgery will be included in the TME group. We define this analysis as a comparison between TME vs. durable NOM. Durable NOM is defined as 3-year disease-free survival. We expect that 70% of patients will complete the QoL assessment at 1 year. This response rate takes into account refusals to complete the QoL

questionnaires, and the approximately 20% of patients who will develop distant disease or die before the 1-year time point. Thus, at 1 year we expect to have information on 94 TME patients and 62 NOM patients.

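### Section 14.3 expects about 20% distant disease or death by one year after TNT, which caps 3-year DFS at 80%, below the 85% hypothesis and the .82 cut-off in 14.1

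*Protocol*

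**What the plan says.** Protocol section 14.1 sets the efficacy premise: "We hypothesize that 85% of patients with LARC treated with TNT and selective NOM will be alive and free of disease at 3 years". Each arm is a single-stage design that "discriminates between 3-year DFS rates of 75% (historical control) and 85% (Study Arms, INCT and CNCT"), and the size is set so that "for 86% power, a two-sided type I error of 5% we will require 101 patients per arm". An arm is worth further study "if the 3-year DFS rate exceeds (based on parametric exponential estimate) .82 (the upper critical value").

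Section 12.0 measures 3-year DFS from randomization as the percentage alive without recurrence. Its only exemption is relapse at the primary site during NOM that is salvaged by TME with negative margins. Distant recurrence and death are not exempt.

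Section 14.3 plans the quality-of-life comparison. "The primary analyses for this aim will use data combined across both treatment arms", and "The primary endpoint will be QoL as measured one year from the end of TNT". It expects 70% of patients to complete the assessment at that time. The stated reasons for the loss are refusals and "the approximately 20% of patients who will develop distant disease or die before the 1-year time point". It then expects data on 94 TME and 62 NOM patients, 156 in all. Section 14.3 gives this sample 80% power for an EQ-5D difference of .07 with a standard deviation of .15.

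**The concern.** The same patients carry two event rates that cannot both hold. The one-year QoL time point comes well before 3 years from randomization. If a fifth of patients have distant disease or have died by then, no more than 80% can be alive and disease-free at 3 years, even with no local recurrence after TME and no later event. That lies below both the hypothesis and the success cut-off.

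A reader cannot tell which rate the sponsor believes. If 20% reflects experience, the 85% hypothesis needs defending. If 85% stands, the attrition figure behind the 70% completion rate, and so behind the stated QoL sample and power, is inconsistent with the design.

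**Working it through.** **1. The plan's own primary figure.** Inputs from 14.1: 75% against 85% at 3 years, 101 per arm, two-sided 5%, uniform accrual over 40 months (A = 3.33 years), 3 further years of follow-up (F = 3), exponential times.
- Hazard λ = −ln(S3)/3: 0.0959 at 75%, 0.0542 at 85%.
- Event probability = 1 − [exp(−λF) − exp(−λ(A+F))]/(λA). Expected events in 101 patients: 36.2 at 75%, 22.5 at 85%.
- Test on the cube root of the hazard, whose standard error is the cube root divided by 3√(events). Critical cube root = 0.4577 × (1 − 1.96/(3√36.2)) = 0.408, which is a 3-year DFS of 0.816.
- Power = Φ[(0.408 − 0.378)/0.0266] = 86.7%, using unrounded values.

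Both stated figures, 86% and .82, are reproduced.

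**2. The ceiling.** This needs no model. S(3 years) ≤ S(t) for any t before 3 years, so 20% events before t gives S(3 years) ≤ 80%. The hypothesis allows 15% events over the whole 3 years and the cut-off allows 18%.

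**3. When the time point falls.** Chemotherapy takes 15–16 weeks and CRT 5–6 weeks (section 4.2), with a gap of 0–8 weeks between them (section 9.3.1). TNT therefore ends 20–30 weeks after treatment start. Adding 52 weeks gives 72–82 weeks, or about 17–19 months. Any lag between randomization and treatment start adds a little.

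**4. Event rates by then that agree with 14.1.** With exponential times, events by month t = 1 − S3^(t/36).
- 85% at 3 years: 1 − 0.85^(18/36) = 7.8% at 18 months (7.2% to 8.2% over 72–82 weeks).
- 75% at 3 years: 1 − 0.75^(18/36) = 13.4% at 18 months (12.4% to 14.0%).

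The stated 20% is about 2.5 times the first (20/7.8) and also above the second.

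**5. Completion rate.** A 70% completion rate with 20% lost to events leaves 10 points for refusals, if the two simply add. On that reading, completion that agrees with 14.1 is about 100 − 10 − 13 = 77% to 100 − 10 − 8 = 82%. If refusals instead apply only to patients still evaluable, the factor is 0.70/0.80 = 0.875, and completion is 0.875 × 0.866 = 76% to 0.875 × 0.922 = 81%. The protocol does not give the split.

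**6. QoL counts and power.** Power = Φ[.07/(.15 × √(1/n1 + 1/n2)) − 1.96].
- Stated counts, 62 and 94: Φ(2.85 − 1.96) = 81.4%, in line with the stated 80%.
- 0.70 × 222 = 155.4, so 156 matches the old total of 222 given in 14.2. It is only 156/325 = 48% of the current total.
- Current counts from 14.3: 0.70 × 196 = 137 and 0.70 × 129 = 90. Power = Φ(3.44 − 1.96) = 93%.

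**The case against.** The strongest defence is that the 20% is a deliberately pessimistic attrition allowance for a questionnaire and not an efficacy forecast. It enters no calculation in 14.1. An allowance may reasonably be worse than the hypothesis, and an error in this direction makes the QoL sample look too small. Both observations stand, and they limit the consequence. They do not remove the contradiction, because the sentence states an expected rate of distant disease and death and lists refusals separately.

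The word approximately does not help. Even 17.5% would clear .82 only with almost no further event up to 3 years, and could never reach 85%. Reading the time point as one year from randomization does not help either, since that also precedes 3 years.

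A reader might infer more: that the 86% power has no basis, or that neither arm could be expected to pass. The documents do not support this. Power is conditional on the stated alternative and reproduces for 75% against 85%. The bleaker forecast comes from extending 20% at 18 months at a constant hazard, 0.80^(36/18) = 64% at 3 years. Section 14.1 adopts the exponential form for its power calculation and words it as time to death. It gives no historical rate at 18 months. The direct implication of 14.3 is only the 80% ceiling. As a rough guide, an arm of 101 with a true 3-year DFS of 80% under that model would still exceed .82 about 26% of the time.

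**Conclusion.** The contradiction holds. Section 14.3 implies a 3-year DFS of at most 80%, which is 5 points below the hypothesis and 2 points below the cut-off in 14.1. This rests only on the DFS definition in section 12.0 and on the order of the time points. No other section reconciles the figures.

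The figures of about 8% and about 13% rest on the exponential assumption and on a time point of about 18 months. They are planning values and not clinical forecasts.

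The primary sample size, cut-off and power are unaffected. What is wrong is the input to the 70% completion rate, and the error understates QoL power. The outdated base of 222 patients matters more for the QoL counts than the attrition rate does. Correcting the 20% alone would leave 14.3 wrong.

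**What to change.** Reconcile 14.1 and 14.3 in one of two ways:
- If the 85% hypothesis stands, replace the 20% in 14.3 with a rate that agrees with it, about 8% under the hypothesis to about 13% under the historical rate, labelled as model-based planning values. State the refusal allowance separately and recompute one-year completion from the two.
- If the 20% comes from data, cite the data and re-justify or restate the 85% hypothesis in 14.1.

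In the same recalculation, apply the completion rate to the 196 TME and 129 NOM patients now stated, and restate the QoL sample size and power. At 70% these are about 137 and 90 patients, with about 93% power for a difference of .07.

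The first route costs wording and one recalculation in 14.3. The second adds a justification or restatement in 14.1. Neither changes trial conduct.

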#### **3.3.2 Rectal cancer response to neoadjuvant therapy**

A number of LARC patients have a pCR to CRT. The rate of pCR ranges from 9% to 44%, depending on the dose of radiation, the use of sensitizing chemotherapy, earlier tumor stage, and the interval between completion of neoadjuvant therapy and surgery. Patients with a pCR have lower rates of tumor recurrence and improved survival compared to non-pCR patients, [35] raising questions about the added value of surgery for these individuals.[12, 36-38] As most of the mortality, morbidity, and long-term sequelae from multimodality therapy are related to excision of the rectum, avoiding TME selectively in patients who obtain a sustained response to CRT will reduce over-treatment and improve QoL.

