| MRI Rectum                               | X   | X    |       | X     |                 | X               |                 | X               |                 | X               |
| CT CAP                                               |     | X    |       | X     |                 | X               |                 | X               |                 | X               |
| CEA levels                               | X   | X    | X     | X     | X               | X               | X               | X               | X               | X               |
| QoL                                      | X   | X    |       | X     |                 | X               |                 |                 |                 |                 |

 +/- 30 days

 After 36 months, CEA will be evaluated every 6 months up to five years, based on NCCN guidelines. MSKCC Only: one to two additional 10 ml EDTA tube(s) of blood will be collected at these time points for research purposes.

 Patients may be contacted by phone for follow-up QoL surveys. The QoL is required for patients who are fluent in reading and speaking English accrued at US and English-speaking Canadian sites. Sites must administer appendices approved by MSKCC's IRB as indicated by the MSKCC IRB/PB watermark.

Procto/sigmoidoscopy and MRI must be completed at treating institution

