### **13.0 CRITERIA FOR REMOVAL FROM STUDY**

All patients will be followed for five years from the last date of treatment. Only patients that choose to withdraw consent will be removed from the study and will no longer be followed.

A patient has the right to withdraw from the study at any time for any reason without prejudice to his/her future medical care by the physician or at the institution.

Every effort will be made to evaluate patients for eligibility prior to enrollment. However, if it is discovered that a patient is found to be ineligible after enrollment, the patient will be removed from the study.

Patients may discontinue protocol treatment without being taken off study. Patients who do not complete protocol treatment will remain on study but will be treated at the discretion of their treating physician. Patients placed on the NOM arm who then undergo TME at a later date will remain on study and be followed according to current NCCN guidelines.

If a patient chooses to discontinue treatment, is removed for clinical reasons, and/or received non-protocol treatment, the study team will continue to follow the patient based on intent-to-treat and collect data for up to five years.

Patients may discontinue treatment for any of the following reasons:

1. Unacceptable toxicity, both severe and unexpected
2. Investigator considers it would be in the patient's best interest to not continue
3. Patient is unwilling or unable to continue study treatment
4. Patient becomes pregnant
5. Lost to follow-up

Patients that discontinue protocol treatment must be followed for existing adverse events (AEs) for 30 calendar days after the last day of study treatment. All Grade  $\geq 3$  events considered unexpected and SAEs (as outlined in 17.2) occurring during that period must be reported to the participating site IRB and MSK per section 17.2. These events must be followed up until resolved, unless the condition is unlikely to resolve because of underlying disease, in the treating physician's opinion. After the 30-day period, patients will be followed for disease and survival status for up to 5 years. Limited information about subsequent treatment will be collected and may include chemotherapy, radiation therapy, and clinical exams, and imaging.

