The primary endpoint of QoL will be assessed using the EQ-5D index, an overall measure of QoL and health ranging from 0 (worst health) to 1 (best health). Comparison will be done using the two-sample t-test. The minimally important difference (MID) for 534 cancer patients in the United States has been estimated to be in the range of .05 to .09 when using ECOG performance status as an anchor (Pickard, Neary, Cella 2007). The standard deviation of the EQ-index was .15 in this patient population. With our sample size of 156, we will be able to detect a difference of .07 with 80% power and type I error of 5%, assuming a standard deviation of .15.

In secondary analyses we will use a t-test to compare the EQ-5D index, measured at 1 year, in patients with durable NOM vs. TME. The differences in EQ-5D index from 1 year to 3 years will also be compared in patients with durable NOM vs TME, using an ANCOVA model that adjusts for variables found to be significantly different by NOM vs TME. Trends in the EQ-5D from baseline, 12, 24, and 36 months will be graphed, and evaluated descriptively.

Similar analyses will be done to study all other patient-reported functional and QoL endpoint.

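### The 1-year NOM versus TME quality-of-life comparison is a t-test on completers, although much of the expected 30% loss is health-related; the direction and size of any bias cannot be settled from the protocol

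*Protocol*

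**What the plan says.** Section 14.3 sets the endpoint: "The primary endpoint will be QoL as measured one year from the end of TNT". The measure is the EQ-5D index, and the method is given in one line: "Comparison will be done using the two-sample t-test". Covariate adjustment appears only in a secondary analysis, for the change from 1 to 3 years. Trends over time are to be graphed and described.

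On numbers, the section states "we expect that 129 patients will obtain complete clinical response and 196 will undergo TME" at the total of 325. On yield it states "We expect that 70% of patients will complete the QoL assessment at 1 year", and it explains the missing part by refusals and by "the approximately 20% of patients who will develop distant disease or die before the 1-year time point". It then projects 94 TME and 62 NOM patients with data.

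Other sections keep these patients under observation. Section 13.0 says "Only patients that choose to withdraw consent will be removed from the study and will no longer be followed" (it also removes patients found ineligible), and it continues data collection on an intent-to-treat basis for up to five years. Section 9.6 schedules surveys at registration, at re-staging and through 36 months, with no stop at recurrence. The NOM follow-up table in section 10.0 adds "Patients may be contacted by phone for follow-up QoL surveys".

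**The concern.** If about 20 of the 30 points of expected loss come from distant disease or death, most of the missing 1-year values would be missing for reasons tied to health. Deaths leave no value to collect. Patients alive with distant disease do have one, and section 14.3 counts them with the deaths when it forecasts yield.

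NOM and TME are not randomized groups. Under section 9.3.2, incomplete responders go to TME, and complete or near-complete responders go to NOM. Section 3.3.2 notes that "Patients with a pCR have lower rates of tumor recurrence and improved survival compared to non-pCR patients". Higher distant failure in TME is therefore plausible. If those patients go unsurveyed, the TME mean is computed on a healthier remainder.

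The t-test can do nothing about this. A patient who answered at registration, re-staging and 3-6 months but not at 1 year contributes nothing, although the earlier scores carry information on the missing one. What is at stake is the primary endpoint of secondary objective 2.

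**Working it through.** **The plan's own figure.** Inputs from section 14.3: 94 TME, 62 NOM, SD .15, 80% power, type I error 5% (taken as two-sided).

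- Detectable difference = (1.960 + 0.842) × .15 × √(1/94 + 1/62) = .0688. Power at .07 is 81.4% (80.9% with the noncentral t). The stated .07 reproduces.
- Retention implied by the counts: 94/196 = 48.0% and 62/129 = 48.1%. The plan uses one fraction for both groups.
- That fraction is not 70%. Seventy percent of 196 and 129 is 137 and 90, total 227, while 156 is about 70% of the earlier total of 222 (155.4). This is a separate inconsistency to correct. At 137 and 90 the detectable difference is .057 and power at .07 is 93%.

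**Size of a possible bias.** The protocol does not split the 20% by group or into deaths and survivors, and it gives no EQ-5D decrement for distant disease. These are therefore assumptions:

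- p = probability of distant disease or death by the 1-year point: 10-15% in NOM and 23-27% in TME. Weighted over 129 and 196, 15%/23% pools to 19.8% and 10%/27% to 20.3%, in line with the plan's 20%.
- a = share of these still alive: .5 to .8.
- d = EQ-5D decrement with distant disease: .10 to .20.
- Every living patient with distant disease is missing at 1 year, and other missingness is unrelated to health.

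The share of a group's survivors who have distant disease is s = p·a / (1 − p(1 − a)). Leaving them out shifts the NOM minus TME difference against NOM by d × (s_TME − s_NOM).

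- Low end (p = .15/.23, a = .5, d = .10): s_NOM = .075/.925 = .081 and s_TME = .115/.885 = .130. Bias = .10 × .049 = **.005**, or 7% of .07.
- High end (p = .10/.27, a = .8, d = .20): s_NOM = .080/.980 = .082 and s_TME = .216/.946 = .228. Bias = .20 × .147 = **.029**, or 42% of .07.

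**Sensitivity.** Here all of the 20% are taken as alive, so the bias is d × (p_TME − p_NOM), with the pooled rate held at 20%.

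| NOM / TME | d = .05 | d = .15 |
|---|---|---|
| 25% / 16.7% | −.004 | −.012 |
| 20% / 20% | 0 | 0 |
| 15% / 23.3% | .004 | .012 |
| 10% / 26.6% | .008 | .025 |
| 5% / 29.9% | .012 | .037 |

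The most extreme combination tried, 5%/29.9% with d = .20, gives just under .05.

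**Is 20% realistic?** Assume the 1-year point falls 1.5 to 2 years after randomization and DFS is exponential. A 3-year DFS of 85% then gives 1 − .85^(1.5/3) = 7.8% to 1 − .85^(2/3) = 10.3% events of any kind, and 75% gives 13.4% to 17.5%. The plan's 20% is above all of these. With a pooled 10%, the values in the table halve.

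**The case against.** The strongest reply is that section 14.3 contains no exclusion. The 70% figure projects how many surveys will come back. It defines no analysis set and tells no one to stop surveying after recurrence. A patient with metastases who returns the 1-year survey enters the t-test as written, and sections 9.6, 10.0 and 13.0 keep that patient on schedule. This stands. A reader might infer that the plan removes the sickest patients, but the documents do not support that.

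Nor do they support a conclusion that the comparison flatters TME. The protocol applies one retention fraction to both groups. The statement in section 3.3.2 compares patients with and without pathologic complete response, which is a different split. NOM also takes near-complete responders, section 3.5 notes residual cancer cells in some clinical complete responders, and the primary analysis keeps NOM cross-overs in NOM. More distant failure in TME remains plausible but unproven.

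A third reply is that missing-data methods usually belong in the statistical analysis plan, which is not at hand, and that a mixed model assumes missing at random and can extrapolate past death. The limits of the model are real, so the fix must include a sensitivity analysis and separate reporting of deaths. But the protocol itself names the test for this endpoint, so the choice of test is open to review here.

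**Conclusion.** The point holds as a weakness of the named method. The plan expects 30% missing 1-year values, attributes much of that loss to distant disease or death, and analyses the remainder with a test that uses none of the EQ-5D data already scheduled before 1 year. The pooling of living patients with deaths in the forecast also sits awkwardly beside sections 10.0 and 13.0 and should be clarified.

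A definite bias toward TME is not shown. The range of .005 to .029 rests entirely on assumed group rates, survival shares and decrements. It lies below the lowest minimally important difference of .05. It goes to zero with equal loss, changes sign if NOM loses more, and is roughly halved if the true event rate is nearer 10%. It could still be a material part of the .07 difference that the comparison is sized for, and nothing in the protocol shows it to be negligible. The change is worth making because a better analysis uses data already being collected.

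**What to change.** In section 14.3:

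1. Make the primary 1-year NOM minus TME contrast come from a mixed model for repeated measures on all collected EQ-5D assessments. Use the registration and re-staging surveys as baseline information, since they precede the grouping, and define group by initial assignment. Measure time from the end of TNT, the origin of the endpoint, because section 9.6 restarts the survey cycle for NOM patients who later undergo TME.
2. State, in line with sections 10.0 and 13.0, that living patients with distant disease stay on the survey schedule, by phone if needed, and are analysed.
3. Report 1-year completion and reasons for missing surveys by NOM and TME. Report deaths before 1 year separately by group and do not count them as missing questionnaires.
4. Add one missing-not-at-random sensitivity analysis, because the mixed model assumes missing at random. One option is to lower the imputed 1-year scores of living non-completers with distant disease over a stated range.

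The cost is a slightly more complex analysis, some wording, and some surveys by phone that the schedule already provides for.

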Based on previous data, we anticipate a 20% NOM in the INCT arm, and 35% in the CNCT arm, after 3 years. The proportion of patients initially entered in the NOM protocol will be higher, but some will later relapse and require TME. For this reason, we anticipate that the proportion of patients with NOM at 3 years will be close to the pCR rates observed in previous studies. We estimated that the 222 patients required for the primary aim would be sufficient to detect differences in organ preservation rates. Our preliminary results indicate that the proportions of patients selected for NOM based on tumor response after completion of neoadjuvant therapy are much greater than expected: 66% in one arm and 79% in the other. Although many of these patients may eventually experience tumor regrowth requiring total mesorectal excision, the proportions of patients with a preserved rectum 3 years after diagnosis are likely to be greater than the original estimates. Therefore, based on the new information, we plan to increase accrual to 325 patients. There is limited information regarding treatment compliance and adverse events in patients who have received more than 4 or 6 cycles of INCT or CTNT. Therefore, these secondary objectives are considered exploratory. If both arms meet the endpoint in primary objective, we plan to use NOM rate to determine the more promising regimen using a “pick the winner” strategy. We will calculate the number of patients treated with NOM who are alive and free of disease 3 years following the start of the study. We will require at least 20 NOM patients in each arm to employ the following strategy: If there is a difference of 5 NOM patients between arms, the arm with more NOM patients will be deemed the winner. With 101 patients in each arm, 20% NOM in patients treated with INCT and 30% in patients treated with CNCT, we will have an 83% probability of selecting CNCT, a 1% probability of selecting INCT, and a 16% probability of considering the study inconclusive.

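### Section 14.3 was only partly updated for 325 patients: its expected 156 quality-of-life completers and detectable difference of .07 match the earlier total of 222 and a 40% NOM share

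*Protocol*

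**What the plan says.** Section 14.1 raises the total: "Based on this new information, we plan to increase accrual to 325 patients". Section 14.2 gives the earlier figure, "We estimated that the 222 patients required for the primary aim would be sufficient to detect differences in organ preservation rates", and explains the increase by the share of patients selected for NOM after neoadjuvant therapy, which was well above expectation: "66% in one arm and 79% in the other".

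Section 14.3 sizes the quality-of-life comparison from the new total: "With a total of 325 patients accrued, we expect that 129 patients will obtain complete clinical response and 196 will undergo TME". It then sets the completion rate: "We expect that 70% of patients will complete the QoL assessment at 1 year". By its own account this rate already covers questionnaire refusals and the "approximately 20% of patients who will develop distant disease or die before the 1-year time point". From these premises it draws the counts: "Thus, at 1 year we expect to have information on 94 TME patients and 62 NOM patients". The power statement follows: "With our sample size of 156, we will be able to detect a difference of .07 with 80% power", at a 5% type I error and a standard deviation of .15.

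The primary quality-of-life analysis keeps patients who start on NOM and later have TME in the NOM group.

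**The concern.** The one-year counts are presented as a consequence of 325 patients and 70% completion, and they are not. The starting group sizes add up to the new total, while the completers, the sample of 156 and the detectable difference appear to belong to the old one.

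The split is a second problem. A 40% NOM share is hard to reconcile with 66% and 79% in the preceding section, particularly as the primary analysis groups patients by initial management.

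At stake is the sample-size justification for the designated primary quality-of-life endpoint. As written, it describes an amount of data and a balance between groups that the enlarged trial is not expected to have.

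**Working it through.** **Inputs.** From 14.3: 129 NOM, 196 TME, 70% completion, 94 TME and 62 NOM completers, SD .15, 5% type I error, 80% power, two-sample t-test. From 14.2: earlier total 222; NOM selection 66% and 79% by arm. Section 14.3 does not say whether the test is two-sided; two-sided is assumed here.

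**Formula.** Detectable difference = (1.960 + 0.842) × SD × √(1/n₁ + 1/n₂).

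**1. The plan's own .07.** With 94 and 62: 2.802 × .15 × √(1/94 + 1/62) = .0688 (.0692 with the noncentral t). Power for .07 is 81%. So .07 is reproduced for 156 patients.

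**2. The counts from the stated premises.**
- 0.70 × 196 = 137.2 TME
- 0.70 × 129 = 90.3 NOM
- 0.70 × 325 = 227.5 in total

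The stated counts imply 94/196 = 48.0%, 62/129 = 48.1% and 156/325 = 48.0% completion. Taking a further 20% off the 70% gives 0.56 × 325 = 182 (110 + 72), which is not 156 either.

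**3. Where 156 comes from.** 0.70 × 222 = 155.4. Applying the same split (129/325 = 39.7% NOM) to 222 gives 88.1 NOM and 133.9 TME. Seventy percent of these is 61.7 and 93.7, which round to 62 and 94. The link to 222 is an inference, but both groups match.

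**4. Correcting the completion step only.** 137 and 90: 2.802 × .15 × √(1/137 + 1/90) = .057. Power for .07 is 93%.

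**5. Correcting the split as well.** Take 325 patients and 70% completion. With one arm at 66% and the other at 79%, the overall NOM share lies between those values; equal arms give (66 + 79)/2 = 72.5%.

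| NOM share | NOM / TME of 325 | NOM / TME completers | Detectable difference (normal; t) | Power for .07 |
|---|---|---|---|---|
| 66% | 214.5 / 110.5 | 150 / 77 | .0588; .0591 | 92% |
| 72.5% | 235.6 / 89.4 | 165 / 62.6 | .0624; .0627 | 88% |
| 79% | 256.8 / 68.3 | 180 / 48 | .0684; .0687 | 82% |

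TME is the smaller group across the whole range, the reverse of 94 against 62.

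**The case against.** The strongest reply is that nothing is lost. The sample was enlarged for organ preservation, not for quality of life. Every corrected detectable difference is no worse than .07 and lies inside the .05–.09 range of minimally important differences that the protocol cites. No endpoint, test or decision rule depends on 156. This stands, and it limits the point to an outdated planning statement for a secondary objective. It does not make the derivation in 14.3 correct.

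A second reply is that many NOM patients will later need surgery, so 40% could be a fair eventual share. That does not rescue the split for the primary quality-of-life comparison, which keeps cross-overs in NOM; initial selection is the relevant rate. It does hold for the secondary analysis, where cross-overs move to TME. Their number at the new rates is unknown, so the reversal of group sizes is shown only for the intent-to-treat comparison.

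Third, the replacement counts are uncertain. The 66% and 79% are preliminary and given without denominators, 72.5% assumes equal arms, and section 10 requires the questionnaires only of patients fluent in English at US and English-speaking Canadian sites. These are reasons to give a range. They do not explain 94 and 62, because 14.3 attributes the 70% to refusals and to distant disease or death alone.

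A reader might infer more than the protocol supports:
- **Near-complete responders omitted.** Section 9.3.2 sends them to NOM, while 14.3 labels the 129 as complete responders. But 129 + 196 = 325, so 129 can only be the whole non-TME group. The label is loose; no category is missing.
- **The 20% allowance contradicts the primary hypothesis.** The 85% three-year DFS is a target, against a historical 75%. A missing-data allowance may be more pessimistic than either. It is already inside the 70%, so changing it alone alters no count.
- **Survey effort will go to the wrong group.** Nothing in the protocol allocates survey effort by expected group size.
- **The 56 TME / 24 NOM split in 14.4 needs the same update.** That split is of final treatment, so initial selection rates should not be carried into it.

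**Conclusion.** The point holds as an internal inconsistency with conservative consequences. From its own premises, 14.3 should expect about 137 TME and 90 NOM completers (227), not 94 and 62 (156), a shortfall of about 71 patients. Its 40% NOM share also does not use the 66% and 79% reported in 14.2. The .07 is correctly calculated for 156 but is out of date.

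A reader might conclude that the quality-of-life aim is underpowered. The figures show otherwise: at 66–79% NOM and 70% completion, the detectable difference is about .059–.069, and with equal arms about .063 with 88% power for .07. These results assume SD .15 in both groups, a two-sided 5% test, 80% power, 70% completion in both groups, and preliminary NOM rates that persist to full accrual. Lower completion, for example because of the English-language requirement, would widen the detectable difference.

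**What to change.** In section 14.3, replace 129/196, 94/62, 156 and .07 together. Changing only 94/62 to 137/90 would leave the conflict with 14.2. State:
- **Group sizes for 325 patients** at the observed NOM selection rates: about 215–257 NOM and 68–111 TME, noting that the rates are preliminary.
- **Expected completers at 70%:** about 150–180 NOM and 48–77 TME. If a single planning value is wanted, equal arms give about 165 NOM and 62–63 TME.
- **Detectable difference:** about .059–.069, or about .063 with equal arms, with SD, sidedness and power stated.
- **Balance:** TME is then the smaller group in the intent-to-treat comparison.
- **Completion rate:** whether the 70% allows for the questionnaires being required only of English-fluent patients at US and English-speaking Canadian sites.

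The cost is protocol wording only. No treatment, assessment schedule, endpoint or test changes.
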